### **9.2.2 Assessment of secondary outcomes**

The secondary outcomes are the incidence of ischaemic stroke or systemic embolism and myocardial infarction. Information about secondary outcomes will be identified during a follow-up visit at 2,5 and 10 years.

Patients will be called by the study investigator. A structured script will be used to guide a conversation to obtain information on secondary outcomes. Information about deaths occurring during the study period will be obtained from the Swiss population register.

## **9.3 Procedures at each visit**

### **9.3.1 Baseline visit**

A research nurse will evaluate every patient in the medicine department of the hospital Fribourg for the study enrollment according to the exclusion criteria. Selected patients will receive written and verbal information from the study nurse and then be invited to sign a written consent.

Baseline assessment of all study patients will include the following: a analysis of patient demographics (age, gender), concomitant diseases (hypertension, dyslipidemia, diabetes, heart failure, vascular disease, previous stroke/TIA/thrombo-embolism), calculation of clinical score for atrial fibrillation stroke risk (CHA2DS2-VASc score), and previous symptoms probably related to undetected paroxysmal AF (such as intermittent breathlessness, palpitations, chest pain).

### **9.3.2 Daily visit**

Patients allocated to the treatment group will undergo daily monitoring with the handheld Zenicor ECG. Participants will place their thumbs on the device at least twice daily and whenever they notice palpitations.

### **9.3.3 Cardiological visit**

All individuals with newly detected AF are offered a individualized medical visit by a cardiologist to assure an adequate treatment. Individual net benefit from OAC treatment will be assessed by a 12

lead-ECG, echocardiography and blood sample analysis (with renal function, electrolytes, lipid profile).

#### **9.3.4 Follow-up**

Follow-up will be carried out at 2, 5 and 10 years after the diagnostic by a medical interview by telephone. The following data will be assessed: ischemic stroke or systemic embolism and myocardial infarction.

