### **3.6 Risks / Benefits**

Guidelines strongly and uniformly recommend anticoagulation in patients with AF in order to reduce the thromboembolic risk. The benefits of oral anticoagulant therapy are directly proportional to the underlying stroke risk as measured by hypertension, age, diabetes mellitus, congestive heart failure, prior stroke, vascular disease, and gender (CHA2DS2 -VASc score). Despite the documented benefits of anticoagulation in high-risk patients, bleeding complications are a common concern with the use of anticoagulant. The factors associated with a higher bleeding risk are similar to those conferring a higher thromboembolic risk. Nevertheless, it is the patients with the highest thromboembolic risk that benefit the most from oral anticoagulant therapy.

A potential risk of the Detect-AF study is the overdiagnosis of atrial fibrillation. This might lead to a non-indicated anticoagulant treatment and might expose the patients to an unnecessarily increased bleeding risk.

However, every case of new AF diagnosed by use of the screening method will be reviewed by two independent cardiologists. In case of uncertainty, additional recordings, e.g. Holter or R-Test will be performed.

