### **5.2 Secondary Outcomes**

Secondary outcomes are death, cardiovascular death, stroke, transient ischemic attack or systemic embolism, myocardial infarction and bleeding at 2, 5, and 10 years after study enrollment.

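### Sections 9.2.2 and 9.3.4 conflict with Section 5.2 and the synopsis on which secondary outcomes are collected and from what date follow-up runs

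*Protocol*

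**What the plan says.** Section 5.2 gives the long list: "Secondary outcomes are death, cardiovascular death, stroke, transient ischemic attack or systemic embolism, myocardial infarction and bleeding at 2, 5, and 10 years", counted from study enrolment. The synopsis names the same outcomes. Its row on measurements and procedures assigns them to the clinical follow-up of every enrolled patient at 2, 5 and 10 years.

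Section 9 is narrower. Section 9.2.2 states: "The secondary outcomes are the incidence of ischaemic stroke or systemic embolism and myocardial infarction". It describes a telephone call guided by a structured script and adds: "Information about deaths occurring during the study period will be obtained from the Swiss population register". Section 9.3.4 gives the timing as "Follow-up will be carried out at 2, 5 and 10 years after the diagnostic by a medical interview by telephone" and then the content: "The following data will be assessed: ischemic stroke or systemic embolism and myocardial infarction".

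Two other sections bear on this. Section 3.6 describes overdiagnosis of AF as a potential risk, because non-indicated anticoagulation "might expose the patients to an unnecessarily increased bleeding risk". Section 11.3.2 compares event-free survival between the randomised groups at 2, 5 and 10 years.

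**The concern.** What is asked in the call, of whom, and from what date are data-collection instructions. A statistical analysis plan cannot recover events that were never recorded, so the conflict has to be settled in the protocol.

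**Content.** The short list appears twice, and 9.2.2 presents it as the definition of the secondary outcomes. A reader who builds the script from Section 9 would record the thromboembolic outcomes that screening aims to prevent. The same reader would not record bleeding, the outcome through which 3.6 expects overdiagnosis to do harm. Limiting stroke to ischaemic stroke also removes haemorrhagic stroke. The benefit side of the comparison would then be measured and the harm side would not.

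**Clock.** A comparison of event-free survival between arms needs an origin that exists for every randomised patient and does not depend on what happens after randomisation. A date of AF diagnosis fails on both counts: most patients will not have one, and the intervention is designed to change how many do.

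**Working it through.** **Step 1. Outcomes and anchors side by side.**

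| Item | 5.2 | Synopsis | 4.3 | 9.2.2 | 9.3.4 |
|---|---|---|---|---|---|
| Death, any cause | yes | yes | yes | yes, register | no |
| Cardiovascular death | yes | yes | no | no source for cause | no |
| Stroke | any | any | ischaemic | ischaemic | ischaemic |
| TIA | yes | yes | no | no | no |
| Systemic embolism | yes | yes | yes | yes | yes |
| MI | yes | yes | yes | yes | yes |
| Bleeding | yes | yes | no | no | no |
| Start of the 2, 5 and 10 years | enrolment | not given in the procedures row; all enrolled patients | not given | not given | the diagnostic |

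The list in 4.3 is introduced as examples, so it is weaker evidence than 9.2.2 and 9.3.4. Counting TIA and systemic embolism separately, 5.2 names seven outcomes. Section 9 covers three of them in full (all-cause death, systemic embolism, MI), one in part (stroke) and three not at all (cardiovascular death, TIA, bleeding). Section 10 sets up no collection of bleeding either.

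**Step 2. The plan's rates.** Section 11.2 assumes detection of 1% in the control group and 3% in the intervention group, and plans 745 per group, raised to 800. The usual two-proportion formula with unpooled variance (two-sided α 0.05, power 80%) gives

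n = (1.960 + 0.842)² × (0.01×0.99 + 0.03×0.97) / 0.02² = 7.849 × 0.0390 / 0.0004 ≈ 765.3, so 766 per group.

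That is within 3% of 745, and power at 745 is about 79%. The stated rates are therefore consistent with the plan's size and can be carried into the next step. Nothing in this point turns on the sample size itself.

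**Step 3. Who would have a starting date, by reading of 9.3.4.**

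- *The AF diagnosis:* 800×0.01 + 800×0.03 = 8 + 24 = 32 of 1,600, or 2%. The other 1,568 (98%) have no date. With 745 per group: 7.45 + 22.35 = 29.8 of 1,490, again 2%.
- *The screening recordings:* the 800 intervention patients have a date and the 800 controls have none, so 50% lack one.
- *Enrolment, as in 5.2:* all 1,600 have a date.

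On the first reading the dated patients would also split 24 to 8 between arms, and each would be selected by detection.

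**Step 4. Timing.** This version is dated 13.08.2019. With the first participant planned for 01.03.2018, the first two-year calls fall in about March 2020, some six months later.

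**The case against.** The strongest reply is that the protocol already contains the right instruction. The synopsis row on procedures is operational: it sends the full list, with bleeding and TIA, to follow-up of all enrolled patients. Section 9.2.2 says the script will gather information on secondary outcomes, and 5.2 defines those to include bleeding. The script and the case report forms (Appendix 4) are not shown and may hold every field. This stands as far as it goes. A reader might infer from Section 9 that bleeding will certainly go unrecorded, and the documents do not support that. They show two incompatible instructions and no rule for which governs. An adequate form would not remove the conflict from the protocol.

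On the clock, 9.3.4 does not say AF diagnosis. In the study schedule only the investigations column is restricted to patients with newly diagnosed AF; the follow-up column is not. Section 9.3.4 also sets when calls are made and does not expressly define the origin for the survival analysis. All of this stands. It would therefore be wrong to state as fact that 98% of patients have no time zero; that figure belongs to one reading. The placing of 9.3.4 directly after the cardiological visit for patients with new AF makes that reading natural, and the main alternative still leaves the control arm without a date. For patients whose AF is found in hospital, diagnosis and enrolment should lie close together, so the harm is to everyone else.

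Three further limits hold. Section 3.6 calls bleeding a potential consequence and pairs it with review by two cardiologists, and Section 10.1 names other harms (anxiety, cost, false reassurance), so the text does not make bleeding the trial's main harm. All-cause death is not at risk, because the register covers it. The primary outcome is untouched.

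**Conclusion.** The point holds as an internal contradiction on both the content and the timing of follow-up. Its consequences are conditional:

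- If Section 9 governs, three of the seven outcomes in 5.2 (cardiovascular death, TIA, bleeding) have no collection step, and a fourth (stroke) is narrowed to ischaemic events.
- If 9.3.4 sets the clock, between 50% and 98% of patients have no starting date, depending on what the diagnostic means. The comparison in 11.3.2 cannot be run from such a date.

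The 2% and 98% figures assume that the rates in 11.2 apply as proportions of the 800 patients per arm, as the synopsis presents them; 11.2 calls them annual. Later detections would move the figures but would not give every patient a date.

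The matter should be settled before the first two-year calls. On the planned dates, a correction made by then loses nothing. After that, events not asked about in one call depend on recall at the next, three or five years on.

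**What to change.** Reconcile 9.2.2 and 9.3.4, and the examples in 4.3, with 5.2 and the synopsis:

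1. State one list of secondary outcomes and refer to it from every section.
2. Use the same telephone script in both arms, covering every non-fatal outcome in 5.2 (any stroke, TIA, systemic embolism, MI, bleeding), with the date of each event.
3. Replace the diagnostic date in 9.3.4 with one date that every patient has. Section 5.2 uses enrolment. Randomisation follows on enrolment under 2.6 and 7.3 and would serve equally well. Name one and use it both for scheduling calls and as time zero in 11.3.2.
4. Either name a source for cause of death or drop cardiovascular death as an outcome. The register is described only as a source of information about deaths.
5. Check the script and the case report forms against the agreed list.

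A bleeding scale and the recording of anticoagulant use may be worth having, but they go beyond reconciliation and could sit in the analysis plan or the forms.

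The cost is amendment wording and slightly longer calls that are already planned. If cardiovascular death is kept, obtaining cause of death is real extra work.

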## **10. SAFETY**

### **10.1 Definition and Assessment of safety related events**

Active screening for AF can lead to both false positive results and false negative results.

It can increase anxiety and costs for further diagnostics in false positive cases or provide a false sense of security and lead to complacency relating to AF-related symptoms in false negative cases.

### **10.2 Reporting of Safety related events**

Health hazard that require measures will be reported to the Sponsor-Investigator within 24 hours upon becoming aware of the event and within 2 days to the local Ethics Committee.

## **11. STATISTICAL METHODS**

Categorical variables will be reported as counts and percentages; continuous variables will be reported as mean and SD or as median with 25% to 75% interquartile range according to their distribution. Normality will be assessed by visual inspection of histograms, the computation of Q-Q plots and the shapiro-wilk test. Categorical variables will be compared using chi-square or Fisher's exact test as appropriate. Continuous variables will be analyzed using the Student's t-test or the Wilcoxon rank-sum test according to their distribution. Survival free from the occurrence of clinical end points will be compared using the log-rank test and plotted as Kaplan-Meier survival functions. All statistical analyses will be performed using dedicated software (Stata version 13, StataCorp LP, College Station, Texas) at a 2-tailed significance level of  $\alpha = 0.05$ .

### **11.1 Hypothesis**

The null hypothesis to be rejected is that there is no difference with regard to the percentage of newly detected AF in the control and the intervention group.

### **11.2 Determination of Sample Size**

Based on previous research, the expected annual detection rate is 3% in the Zenicor group and 1% in the control group. The inclusion of  $n=745$  patients per group would yield a power of 80% and a significance of  $\alpha = 0.05$  to detect that difference. In order to account for ineffective measurements, post-inclusion drop-outs or other unforeseen drop-outs, we seek to include  $n=800$  patients per group.

### **11.3 Planned Analyses**

#### **11.3.1 Primary Analysis**

The primary analysis pertains to the proportion of newly detected atrial fibrillation. The primary analysis will compare the proportion of newly detected AF between the intervention and the control group. Univariate methods (Chi-Test) will be employed. If a significant difference in baseline characteristics will be observed, then logistic regression will be performed in order to correct for baseline imbalances.

#### **11.3.2 Secondary Analyses**

A secondary analysis will focus on subgroups. Pre-specified subgroups comprise gender, age, diabetes, hypertension, ischemic heart disease, congestive heart disease and all subcategories of the CHADS-Vasc Score. Additional analysis will be performed on clinical follow-up. Event-free survival between the intervention and the control group will be compared at 2, 5 and 10 years according to the Kaplan-Meier method. Adjustment for eventual imbalances will be performed by using Cox

proportional hazards given that the data do not violate the proportionality assumption.

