### **3.7 Justification of choice of study population**

The 2016 ESC-Guidelines for the management of atrial fibrillation underscore the importance of the

evaluation of systematic AF screening in at-risk populations. Hospitalized patients constitute such an at-risk population because of their older age and their often multiple comorbidities predisposing to AF. To our knowledge, this is the first study evaluating a systematic screening method to detect atrial fibrillation in hospitalized patients.

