## **7. STUDY POPULATION**

### **7.1 Eligibility criteria**

All patients admitted to the Internal Medicine Department at Hospital Fribourg throughout the study period will be screened for study enrollment. Patients with known or previously documented AF, patients with a cardiac pacemaker, and implantable cardioverter-defibrillator or intra-cardiac monitoring device will be excluded from the present trial. Patients with an estimated life expectancy of < 6 months will likewise be excluded. Patients unable or unwilling to provide written-informed consent, to participate in the study procedures or in clinical follow-up will be excluded from the trial.

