## **11.4 Handling of missing data and drop-outs**

Missing data will be omitted pairwise from the analyses. Whenever data is missing, it will be explicitly stated in the final results of the study. Missing data arising from a loss to follow-up will be censored. The number of drop-outs will be provided in a flow-chart along with the reasons for said drop-out.

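### Kaplan-Meier is the only time-to-event estimator named for the 2-, 5- and 10-year outcomes and the handling of death is not stated; if competing deaths are censored, the risks of stroke/TIA/embolism, myocardial infarction, bleeding and cardiovascular death will read too high

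*Protocol*

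**What the plan says.** Protocol section 5.2 defines the long-term endpoints: "Secondary outcomes are death, cardiovascular death, stroke, transient ischemic attack or systemic embolism, myocardial infarction and bleeding at 2, 5, and 10 years". Death and cardiovascular death are separate items. Section 9.2.2 gives a shorter list, and describes its target as the incidence of ischaemic stroke or systemic embolism and of myocardial infarction.

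Two places fix the analysis. Section 11: "Survival free from the occurrence of clinical end points will be compared using the log-rank test and plotted as Kaplan-Meier survival functions". Section 11.3.2: "Event-free survival between the intervention and the control group will be compared at 2, 5 and 10 years according to the Kaplan-Meier method". For adjusted comparisons, section 11.3.2 adds: "Adjustment for eventual imbalances will be performed by using Cox" proportional hazards. No other time-to-event estimator is named.

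The only censoring rule is in section 11.4: "Missing data arising from a loss to follow-up will be censored". Deaths are to be captured separately; section 9.2.2 says: "Information about deaths occurring during the study period will be obtained from the Swiss population register". The protocol does not say whether, in the analysis of stroke, myocardial infarction, bleeding or cardiovascular death, a death from another cause is an event, a censoring or a competing event.

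**The concern.** A patient who dies cannot later have a stroke, an infarction or a bleed, and a patient who dies of a non-cardiovascular cause cannot later die of a cardiovascular one. A Kaplan-Meier curve for one of these outcomes alone has to censor such patients. One minus the curve then estimates the risk in a hypothetical setting without the competing deaths, which is higher than the proportion of patients who actually have the event.

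The size of the difference depends on mortality over the follow-up. The protocol gives no death rate, but section 3.7 describes the population in these terms: "Hospitalized patients constitute such an at-risk population because of their older age and their often multiple comorbidities predisposing to AF". The only exclusion based on prognosis, in section 7.1, is short: "Patients with an estimated life expectancy of < 6 months will likewise be excluded". Follow-up runs to 10 years, so substantial mortality is to be expected.

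What is at stake is the absolute figures: the risk in each arm at each time point, and any arm difference in stroke or bleeding read from the curves. Those are the figures by which a reader would weigh the benefit of screening against its harm.

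**Working it through.** **Plan's own figure.** There is none to reproduce. The protocol states no event rate, death rate or power for the clinical outcomes, and its sample-size figures concern the primary outcome only.

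**Step 1: the two possible readings.**

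- *Each listed outcome has its own curve.* Competing deaths must be censored. Otherwise the cardiovascular-death curve would be the all-cause-death curve, and the stroke curve would be stroke-or-death.
- *Event-free survival is a composite that includes all-cause death.* Kaplan-Meier is then right for the composite, but it gives no estimate of the separate outcomes in section 5.2 or of the incidences named in section 9.2.2.

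**Step 2: size under the first reading.** All rates here are assumptions. Let *e* be the constant yearly rate of the outcome, *d* the constant yearly rate of competing death and *t* the time in years.

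- One minus Kaplan-Meier, death censored: 1 − exp(−e·t)
- Cumulative incidence, death competing: e/(e+d) × [1 − exp(−(e+d)·t)]

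Example with e = 0.02, d = 0.05, t = 10:

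- One minus Kaplan-Meier: 1 − exp(−0.20) = 18.1%
- Cumulative incidence: (0.02/0.07) × [1 − exp(−0.70)] = 14.4%
- Ratio: 1.26
- Composite of event or death: 1 − exp(−0.70) = 50.3%

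Ratio of one minus Kaplan-Meier to cumulative incidence, for e of 1% to 2% per year:

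| Assumed competing deaths per year | 2 years | 5 years | 10 years |
|---|---|---|---|
| 3% | 1.03 | 1.08 | 1.15 |
| 5% | 1.05 | 1.13 | 1.26-1.27 |
| 8% | 1.08 | 1.21 | 1.43-1.44 |
| 10% | 1.10 | 1.27 | 1.56-1.57 |

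The ratio hardly depends on *e*; it is driven by *d* and *t*. For cardiovascular death, *d* is the rate of non-cardiovascular death only, so a lower row applies than for the non-fatal outcomes.

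**Step 3: arm differences.** As an illustration, not a forecast, take event rates of 2% and 1% per year in the two arms and 5% deaths per year in both. At 10 years:

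- One minus Kaplan-Meier: 18.1% − 9.5% = 8.6 percentage points
- Cumulative incidence: 14.4% − 7.5% = 6.9 percentage points

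The difference is inflated along with the risks.

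**Step 4: what is not affected.** The log-rank test and the Cox model with competing deaths censored remain valid comparisons of cause-specific hazards. Kaplan-Meier for all-cause death has no competing event. The primary outcome is a proportion compared by chi-square test.

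**The case against.** The strongest reply is that the protocol never says deaths are censored. A reader might infer that it does, and that the trial will therefore report overstated risks. The text does not support that as a stated fact. Section 11.4 censors only loss to follow-up, and death is itself a listed clinical endpoint, so event-free survival can fairly be read as ending at death. On that reading Kaplan-Meier is correct. This stands, and it makes the point conditional. It does not close it, because the outcomes of sections 5.2 and 9.2.2 then have no time-to-event estimate.

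Second, the protocol promises comparisons and plotted curves and does not say that one minus Kaplan-Meier will be reported as an absolute risk. That is also true, and the hypothesis tests are sound as cause-specific comparisons. But a comparison at 2, 5 and 10 years by this method uses the estimated probabilities at those times, and the plots display them. Section 11 also allows counts and percentages for categorical variables, but does not say whether that covers the follow-up events.

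Third, competing-event handling is often left to an SAP, and one may exist. The point, however, is not a missing detail: the protocol names an estimator that does not suit most of the outcomes listed for it.

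Fourth, the magnitude rests wholly on assumed rates. This is correct; at 3% deaths per year the overstatement is only 15% at 10 years and 3% at 2 years.

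Finally, cumulative incidence does not cure every problem. Non-fatal events come from telephone interviews at 2, 5 and 10 years (sections 9.2.2 and 9.3.4), and no source is named for events in patients who die between calls. That limitation remains with either estimator.

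**Conclusion.** The point holds in conditional form. The protocol names Kaplan-Meier as its only time-to-event estimator for the clinical outcomes and leaves the handling of death open. Either the listed outcomes are analysed separately with competing deaths censored, and their risks are overstated, or death is merged into a composite and those outcomes are not estimated. Both cases call for a change of wording.

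Under the first case, with constant hazards, event rates of 1-2% per year and competing death rates of 3-10% per year, the relative overstatement is about 3-10% at 2 years, 8-27% at 5 years and 15-57% at 10 years. It is minor at the first follow-up and material at the last. The documents do not support going further and saying that deaths will be censored, that the planned tests are invalid, or that the primary outcome or all-cause death is affected.

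**What to change.** In Protocol sections 11 and 11.3.2:

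- Define event-free survival and say how death is handled for each outcome.
- Keep Kaplan-Meier for all-cause death and for any composite that explicitly includes all-cause death.
- For stroke/TIA/embolism, myocardial infarction and bleeding, report the 2-, 5- and 10-year risks and the arm differences with 95% confidence intervals by the Aalen-Johansen cumulative incidence estimator, with death as the competing event.
- For cardiovascular death, do the same with non-cardiovascular death as the competing event.
- Keep the log-rank test and Cox model, labelled as comparisons of cause-specific hazards.

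If an SAP already does this, bring the protocol wording into line with it. The change should be made before the follow-up data are analysed.

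The cost is a few sentences and standard software. Stated absolute risks will be lower than those read from curves that censor death, most visibly at 10 years. Deaths are already to be obtained from the population register. Cause of death is also needed; section 9.2.2 does not say that the register supplies it, but the cardiovascular-death outcome already requires it.
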